## Study design

The LiverCare study is a multi-center mixed-method non-randomised intervention study with a hybrid type 1 effectiveness-implementation design, thus taking a dual focus in assessing clinical effectiveness and implementation [21]. The intervention was developed using a pragmatic design with the aim of utilizing existing infrastructure in the implementation [22]. Furthermore, to ensure a comprehensive understanding of the intervention’s functionality and support potential adaptation or replication, a feasibility study and a mixed-method process evaluation will be conducted.

The study design is guided by the British Medical Research Council (MRC) framework for developing and evaluating complex interventions [23]. Since the MRC guidance does not provide an iterative process or specific research designs, we further utilize the Reach, Effectiveness, Adoption, Implementation, and Maintenance (RE-AIM) Framework, which is efficient for evaluating intervention studies [24]. The RE-AIM framework operates at both the individual level (patients and informal caregivers), and the multiple ecologic level (health care professionals and the centres involved in the intervention).

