### Participants and eligibility criteria

#### Inclusion criteria for patients are as follows

Adult patients with the diagnosis of cirrhosis of any etiology (clinically, radiologically, or histologically confirmed) as the predominant chronic illness.At least one general and one disease-specific palliative care indicator assessed by the Supportive and Palliative Care Indicators Tool (SPICT).Ability to provide informed consent.Ability to read and understand Danish.

SPICT is a needs-assessment clinical tool developed to identify individuals with serious or advanced illness who are at risk of deteriorating health or dying and who may benefit from palliative care [26]. It supports healthcare professionals in recognising potential unmet palliative needs by combining general and disease-specific indicators, although it does not itself determine the exact nature or severity of those needs. In this study, patients were eligible for inclusion if they had at least one general and one disease-specific SPICT indicator.

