### Baseline and clinical data

At baseline, sociodemographic data will be collected on participants’ age, gender, highest completed level of education, employment status, housing conditions, family relations, support received from the primary sector, and complicating factors such as substance abuse issues, social network difficulties, financial problems, and housing instability. Additionally, disease-related information will be gathered, including cirrhosis etiology, year of diagnosis, complications, and comorbidities. At each study visit, the patient’s current clinical status will be assessed with particular attention to the severity of cirrhosis-related complications and overall frailty, evaluated using the Clinical Frailty Scale [33]. Liver disease severity and prognosis will be evaluated by calculating the Child-Pugh and Model for End-Stage Liver Disease (MELD) scores [34, 35].

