### Effectiveness outcomes

#### Primary outcome

*Healthcare system burden*, measured as the number and length of hospital admissions from the initial visit to death or study exit. Data on health care utilisation will be prospectively recorded by registering events since the last visit at each study visit and compared to a recent historic cohort of a similar size from the involved centers.

Hospital admissions will be categorised into three mutually exclusive groups:

*Liver-related admissions*: inpatient stays of ≥ 24 h due to complications of liver cirrhosis, including variceal bleeding and other bleeding related to portal hypertension, hepatic encephalopathy, spontaneous bacterial peritonitis, hepatorenal syndrome, alcoholic hepatitis, ascites, infection, electrolyte imbalances, increasing frailty, sarcopenia, or poor nutritional status.*Non-liver-related admissions*: inpatient stays of ≥ 24 h for conditions not directly related to cirrhosis.*Short admissions*: hospital stays of < 24 h, excluding admissions in which paracentesis is the sole intervention.

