## Sample size and statistical methods

### Sample size

The study aims to include 240 patients and 100 informal caregivers, based on sample size calculations for the most significant outcomes and to accommodate expected attrition.

The Healthcare System Burden will be measured as the number and length of admissions. Patients with cirrhosis spend an average of seven days per year in hospital [39]. Health care utilization data from the intervention group will be compared to a recent historical cirrhosis cohort. For the sample size calculation, we assumed the historical cohort will have an average of seven days in hospital per year and hypothesize that the intervention will cause a reduction of two days/year with an assumed SD of 7 days. Hence, 199 participants are required (STATA BE 18.5). With an estimated attrition rate of 20%, we aim to include 240 patients [40, 41].

Caregiver burden will be measured using the 22-item ZBI (range 0–88). A change of 5 points is considered realistic and clinically relevant. Based on previous studies, this change can be detected with 100 informal caregivers if the standard deviation (SD) of the change is around 14 [35, 36].

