### Statistical methods

All data will be entered into a shared REDCap database [42]. Descriptive statistics for numerical data will be presented as means with standard deviations (SD) for normally distributed variables, or as medians with interquartile ranges (IQR) for non-normally distributed variables. Categorical data will be presented as counts and proportions. For between-group comparisons, unpaired two-sample Student’s *t*-tests will be used for normally distributed numerical data, and the Wilcoxon-Mann-Whitney test for non-normally distributed numerical data. Categorical variables will be compared using the chi-squared test. Differences between groups will be reported as means with standard errors (SE) and 95% confidence intervals (CI) for numerical outcomes, and as odds ratios (OR) with 95% CI for dichotomous outcomes. All statistical analyses will be conducted using Stata Statistical Software, version 16 (StataCorp, College Station, Texas). Missing data will be reported and explored. Where appropriate, multiple imputation techniques will be considered. Both intention-to-treat (ITT) and per-protocol analyses will be conducted to assess robustness of findings.

The cost-effectiveness analysis will include cost and effect. The costs will include intervention-related expenses (e.g. staff time, training, materials) while the effect will include the use of healthcare resources using Danish DRG standard tariffs.

The cost-utility analysis will be based on the EQ-5D-5 L-data and the values will be converted to utility scores using Danish population-based value [43]. These scores will be used to estimate QALYs, which will serve as the measure of effectiveness.

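### Every between-group test named for the comparison with the non-randomised historic cohort is unadjusted, so the crude difference in hospital use may be biased in either direction

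*Protocol article*

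**What the plan says.** The Study design section describes the trial in these terms: "The LiverCare study is a multi-center mixed-method non-randomised intervention study with a hybrid type 1 effectiveness-implementation design". The primary outcome is "measured as the number and length of hospital admissions from the initial visit to death or study exit", and it is to be "compared to a recent historic cohort of a similar size from the involved centers". The Sample size section describes the comparator only in general terms: "Health care utilization data from the intervention group will be compared to a recent historical cirrhosis cohort".

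The Statistical methods section names the tests for between-group comparisons: the unpaired two-sample t-test for normally distributed numerical data, "and the Wilcoxon-Mann-Whitney test for non-normally distributed numerical data. Categorical variables will be compared using the chi-squared test". On reporting it says: "Differences between groups will be reported as means with standard errors (SE) and 95% confidence intervals (CI) for numerical outcomes". Intention-to-treat and per-protocol analyses are the only robustness analyses named.

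On selection into the intervention group, "patients were eligible for inclusion if they had at least one general and one disease-specific SPICT indicator". Patients must also be able to consent and to read Danish. They must not be listed for transplantation, be in current contact with specialised palliative care or hospice, or have advanced cancer other than hepatocellular carcinoma.

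On prognostic data, the Baseline and clinical data section says: "Liver disease severity and prognosis will be evaluated by calculating the Child-Pugh and Model for End-Stage Liver Disease (MELD) scores". It also lists age, gender, aetiology, complications, comorbidities and the Clinical Frailty Scale.

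**The concern.** The named tests give an interpretable treatment effect when the two groups are exchangeable apart from treatment. Randomisation would secure that, but this trial has none. Intervention patients passed a palliative-needs screen and a set of exclusions, were able to consent, and chose to take part. The article states none of these conditions for the historic cohort.

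If the cohorts differ in severity, the crude difference in admissions or hospital days contains that difference as well as any effect of the intervention. The standard error and confidence interval measure sampling variation only, so they would give no sign of it. The primary effectiveness conclusion rests on this comparison, and the cost-effectiveness analysis based on admissions would carry the same bias.

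The direction cannot be told from the article. If the patients who consent and attend are fitter, the result could show a benefit that does not exist. If SPICT-positive patients are set against a broader cirrhosis cohort, the result could hide a real one.

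**Working it through.** **Inputs.** From the Sample size section: control mean 7 days/year, reduction 2 days/year, SD 7 days, 199 participants required, 20% attrition, target 240. Alpha and power are not stated; I assume two-sided 5% and 80%.

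**The plan's own figure.** For a crude two-group comparison of means,

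n per group = 2 × (1.96 + 0.84)² × 7² / 2² ≈ 193 (194 with the t distribution).

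The stated 199 is close to this and gives 81% power if it is a per-group number. As a total over both groups it would give 52%. So the sample size fits an unadjusted two-group test with 199 per group, in line with the tests named.

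**Precision.** SE = 7 × √(2/n).

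- n = 199: SE = 0.702 days/year
- n = 192 (240 × 0.80): SE = 0.714 days/year

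**Effect of a case-mix shift b when the intervention does nothing.** P(reject) = Φ(−1.96 + b/SE) + Φ(−1.96 − b/SE). With 199 per group:

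| Assumed shift b (days/year) | P(reject) |
|---|---|
| 0 | 5% |
| 0.5 | 11% |
| 1.0 | 30% |
| 1.5 | 57% |
| 2.0 | 81% |

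With 192 per group and b = 1: 1/0.714 = 1.40, and Φ(−0.56) + Φ(−3.36) ≈ 29%.

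**Effect when the true reduction is 2 days and the shift runs against the intervention.** With b = 1 the expected crude difference is 2 − 1 = 1 day, and power with 199 per group falls from 81% to 30%.

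**How large might b be?** The documents give no figure, so this part is assumption. If the cohorts differ by d SD on a prognostic score that correlates r with hospital days, then b = d × r × 7.

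- d = 0.3, r = 0.3: b = 0.63, which is 32% of the 2-day target; P(reject) = 14% with 192 per group
- d = 0.3, r = 0.5: b = 1.05, which is 53% of the target; P(reject) = 31%
- d and r each from 0.2 to 0.5: b = 0.28 to 1.75; P(reject) = 7% to 69%

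**Search for a safeguard.** The article mentions no regression adjustment, matching, weighting, propensity score or stratification by centre. Nor does it apply the SPICT or exclusion criteria to the comparator. Intention-to-treat and per-protocol sets vary which intervention patients count, and multiple imputation deals with missing values. None of these addresses differences between the cohorts. The Discussion raises heterogeneity between sites but not comparability with the historic cohort.

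**The case against.** The paragraph on tests is generic and covers all numerical and categorical variables. It does not say that adjusted analyses are excluded. A statistical analysis plan may exist, and covariate lists and balance checks are commonly left to it. A reader might infer that the trial will have no adjusted analysis at all. The article does not support that; it supports only that every between-group test it names is unadjusted. The point still stands, because the article is not silent: it states which tests will be used, and they do not suit the design.

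The comparator is recent and comes from the same centres. This does limit centre and calendar differences, although the centre mix could still differ. It does not touch patient selection. How the historic cohort is chosen and how its data are obtained are not described, so similar selection is possible and would shrink the problem.

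The percentages rest on an assumed shift and a normal-theory test. With mean 7 and SD 7 for an outcome that cannot be negative, the data are probably skewed. The plan's own rule would then probably choose Wilcoxon-Mann-Whitney, which these figures do not describe exactly. That objection stands against the exact numbers. It does not remove the bias, since that test adjusts for nothing either.

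**Conclusion.** The concern holds for the published plan: a non-randomised comparison is paired only with unadjusted tests, and the prognostic factors collected are not used in it. The crude difference may be biased in either direction. A reader might infer that the bias favours the intervention, but SPICT-positive patients set against a broader cirrhosis cohort could equally mask a benefit.

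As an illustration of size, a 1-day/year shift, half the target effect, takes the false-positive rate to about 30%, or power from about 81% to about 30%. This assumes SD 7, 192 to 199 per group, two-sided 5% and a normal-theory test. The shift itself is assumed. Over the wider assumed range the false-positive rate runs from 7% to 69%, so the figures show sensitivity and do not predict the actual bias. An analysis plan that is not shown could already provide adjustment.

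**What to change.** 1. **Comparator.** Select the historic cohort with the trial's eligibility and exclusion criteria as far as records allow, and define an index date comparable to the initial visit.
2. **Primary analysis.** Make it covariate-adjusted, by regression or propensity weighting with robust standard errors. Adjust for age, sex, centre, aetiology, MELD/Child-Pugh, complications, comorbidity and hospital days in the year before the index date, obtained the same way in both cohorts. The choice between regression and weighting matters less than fixing it in advance.
3. **Crude tests.** Keep the t-test, Wilcoxon-Mann-Whitney and chi-squared results as supportive.
4. **Limits.** State that unmeasured confounding remains. Adjustment on recorded variables cannot fully remove selection by consent, attendance or SPICT status.

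The cost is wording in the protocol and analysis plan, plus extraction of the same baseline variables and prior-year hospital days for the historic cohort. Most of the covariates are already collected in the intervention group; prior-year hospital days are not on the baseline list and would have to be added. Some covariates will be missing in the historic cohort and need a stated handling rule.

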## Introduction

Worldwide, liver cirrhosis ranks as the 11th most common cause of death. In 2019, it accounted for an estimated 1.48 million deaths, reflecting an 8.1% increase since 2017 [1]. The distribution of cirrhosis etiologies and their prevalence varies across countries, largely due to differences in lifestyle factors such as alcohol consumption, obesity, and the risk of viral hepatitis. In Europe, alcohol-related liver disease (ARLD) is currently the leading cause of cirrhosis-related deaths [2].

Liver cirrhosis is the end stage of chronic liver disease of all causes, resulting from sustained inflammation that progresses to fibrosis and, ultimately, liver failure. The progression of liver cirrhosis is divided into a compensated stage, characterized by an absence of specific symptoms and apparent complications, and a decompensated stage featuring one or more severe complications such as ascites, hepatic encephalopathy, infection, renal dysfunction, and variceal bleeding [3]. At this stage, the patient often experiences fatigue, nausea, malnutrition and increasing frailty due to loss of muscle mass. This transition from compensated to decompensated liver cirrhosis significantly worsens health-related quality of life (HRQoL) scores [4, 5], while median survival decreases dramatically from approximately 12 years to just two years [6, 7]. Patients with decompensated liver cirrhosis experience some of the highest rates of unplanned hospital admissions, with 1.5 to 3 liver-related admissions per year [8–12].

The current management of decompensated liver cirrhosis focus on symptom relief, the prevention of further complications, and, if possible, liver transplantation, which remains the only curative option [7–14]. According to the World Health Organization, palliative care should be integrated alongside life-prolonging medical treatment as part of a cohesive approach to care, focusing on enhancing the quality of life for patients and their informal caregivers facing the challenges of serious illnesses. Palliative care aims to prevent and relieve suffering through early identification, assessment, and treatment of physical, psychosocial, and spiritual symptoms and concerns [15].

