### Intervention elements

The intervention is delivered alongside standard care and integrated into patients’ regular clinical appointments. In all participating settings, standard care involves routine follow-up of patients with cirrhosis by a team of hepatologists and specialised liver nurses. Following an admission due to decompensated cirrhosis, patients are routinely offered planned follow-up in an outpatient clinic.

The initial palliative care conversation is conducted by a hepatologist in collaboration with a specialised liver nurse. Alternatively, the conversation may be conducted solely by the liver nurse. Subsequent conversations are conducted by either a hepatologist or a liver nurse after 4–10 weeks, and at 6, 12, 18, 24, 30, and 36 months, or until withdrawal from the study or death. Extra visits may be scheduled if clinically indicated or if the patient or informal caregivers request additional support or planning.

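### For hospital use, the per-protocol analysis cannot test robustness, because adherence cannot be defined in the historic cohort

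*Protocol article*

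**What the plan says.** The Statistical methods section of the protocol article names two analysis populations and gives their purpose: "Both intention-to-treat (ITT) and per-protocol analyses will be conducted to assess robustness of findings". The article defines neither population.

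The Study design section describes the design: "The LiverCare study is a multi-center mixed-method non-randomised intervention study with a hybrid type 1 effectiveness-implementation design". Under Primary outcome, hospital use is "measured as the number and length of hospital admissions from the initial visit to death or study exit", and it is "compared to a recent historic cohort of a similar size from the involved centers".

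Under Intervention elements, a first conversation is followed by a schedule: "Subsequent conversations are conducted by either a hepatologist or a liver nurse after 4–10 weeks, and at 6, 12, 18, 24, 30, and 36 months". The same sentence ends the schedule with the words "or until withdrawal from the study or death".

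For the between-group comparison, Statistical methods names only unadjusted tests (t, Wilcoxon-Mann-Whitney, chi-squared). The Sample size section works in days per year: a control mean of 7, a hypothesised reduction of 2 and an SD of 7.

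**The concern.** A per-protocol analysis normally asks whether the result holds among those treated as intended, and applies its rule to both groups. Here the intended treatment is a series of conversations that exists in one cohort only. A later document can define the intervention-side set, but it cannot create adherence in patients who were never offered the intervention. The restricted intervention cohort would be set against an unrestricted historic cohort, with no adjustment named.

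The restriction is unlikely to be neutral. Attending a visit at week 4–10 or month 6 requires being alive then. Because conversations are built into regular outpatient appointments, it plausibly also requires being out of hospital and well enough to come. Leaving out patients who missed visits can thus select on hospital use itself, which is the primary outcome. Study withdrawal likewise arises in one cohort only.

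What is at stake is interpretation. If the two analyses agreed, the article's wording would have that reported as robustness. If they disagreed, nobody could say whether adherence or selection was the cause.

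**Working it through.** **Inputs from the article**
- Survival (Introduction): "median survival decreases dramatically from approximately 12 years to just two years". The two-year figure is used here as the median.
- Visit times: week 10 (latest second visit) and month 6. Follow-up is capped at 36 months.
- Hospital use: 7 days/year in controls, with a planned effect of 2 days/year.

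**Assumptions not in the article**
- Exponential survival.
- A bed-day rate in the last 3 months of life that is *m* times the earlier rate, with *m* = 1, 3 or 6.
- A per-protocol set meaning alive at the visit date.
- No intervention effect.

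**The plan's own figure.** The article gives no figure for the per-protocol analysis. Its sample size of 199 is approximately recovered as a per-group number. With two-sided 5% and 80% power assumed, 2 × (1.960 + 0.842)² × 7² / 2² = 192.3, so 193 per group, or 194 with the t distribution. The present point does not depend on this figure.

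**Step 1: how many patients an attendance rule could remove.** The share dead by time *t* in years is 1 − 0.5^(*t*/2).
- Week 10: 1 − 0.5^(0.1923/2) = 6.4%, about 15 of 240.
- Month 6: 1 − 0.5^(0.5/2) = 15.9%, about 38 of 240.

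**Step 2: effect on the comparison.** Simulate 400,000 patients with survival time *T* (mean 2/ln 2 = 2.885 years) and follow-up *F* = min(*T*, 3). Expected days are base × (time outside the last 3 months) + *m* × base × (time inside them). The base is scaled so that total days divided by total person-years equals 7. Compare patients with *T* ≥ 6 months (restricted intervention cohort) with everyone (historic cohort).

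| *m* | Mean of patient rates (days/year): restricted vs all | Pooled rate (days/year): restricted vs all | Total days: restricted vs all |
|---|---|---|---|
| 1 | 7.00 vs 7.00 (0) | 7.00 vs 7.00 (0) | 15.20 vs 13.06 (+2.1) |
| 3 | 7.43 vs 8.83 (−1.4) | 6.83 vs 7.00 (−0.17) | 14.84 vs 13.06 (+1.8) |
| 6 | 7.88 vs 10.77 (−2.9) | 6.65 vs 7.00 (−0.35) | 14.44 vs 13.06 (+1.4) |

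A minus sign is spurious benefit and a plus sign is spurious harm.

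The *m* = 1 totals can be checked by hand. Mean follow-up is 2.885 × (1 − 0.5^1.5) = 1.865 years for all patients, and 0.5 + 2.885 × (1 − 0.5^1.25) = 2.172 years for those alive at 6 months. Multiplying by 7 gives 13.06 and 15.2 days.

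With a week-10 rule and *m* = 3 the shifts are smaller: 8.84 to 8.20 (−0.64) for patient rates, 7.00 to 6.96 (−0.04) pooled, and 13.04 to 13.83 (+0.79) for total days.

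**The case against.** A reader might infer that the per-protocol set keeps only patients who lived long enough to attend, and that it is therefore biased toward benefit. The article supports neither statement.

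- **The set is undefined.** Its definition is commonly left to a full protocol or SAP, and its absence from the article is not the fault raised here. The schedule ends at death, so a patient who has the first conversation and dies in week 3 can count as fully adherent. Under that definition no early deaths are removed and the survival part of the bias is zero. This stands, and it makes the survival argument conditional. It does not remove the one-sidedness: missed visits and withdrawals among living patients would still be excluded in one cohort only.
- **The direction is not fixed.** Under Primary outcome, admissions are counted from the initial visit to death or exit. If those counts are not divided by time, longer survivors accrue more days and the bias runs against the intervention. It favours the intervention only on a per-year scale, and only if bed use rises before death. The article gives no figure for such a rise. This stands in full.
- **The larger numbers depend on the estimator.** A mean of patient-level rates is very sensitive to short follow-up, and the article does not specify it. On pooled person-time the shift is at most about 0.35 days/year, small against 2. This also stands.
- **Scope and weight.** PRO-Pall, EQ-5D-5L and ZBI are analysed as changes from baseline, with no historic comparator described, so the argument does not reach them. The all-enrolled result is reported alongside. Whether that analysis should be called ITT without randomisation is only terminology.

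**Conclusion.** The concern holds for the hospital-use comparison and in conditional form. What is certain from the article is that a per-protocol restriction has no counterpart in the historic cohort. The stated purpose, a check of robustness, therefore cannot be met by such an analysis, however the set is later defined.

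The direction and size of any bias are not certain. They rest on an attendance rule, exponential survival with the article's general two-year median (early mortality in enrolled patients may differ) and the assumed end-of-life multiplier. Under a 6-month rule the bias could be comparable to the planned effect in either direction or close to nil, depending on the outcome scale.

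This affects a supportive analysis and leaves the all-enrolled comparison untouched. It is worth changing but does not undermine the trial.

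**What to change.** For the hospital-use outcome, replace the per-protocol analysis with a supportive landmark analysis under one rule for both cohorts:

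- Keep patients in each cohort who are alive and under follow-up at the same time after time zero, for example week 10.
- Classify intervention patients by the conversations held by then.
- Count admissions, bed-days and person-time only after the landmark.

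The historic cohort needs a time zero for this, but the main comparison needs one too. If the landmark analysis is not wanted, state that no per-protocol result will be presented as a robustness check for the comparison with the historic cohort. Per-protocol analyses of the change-from-baseline outcomes can stay.

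The cost is a change of wording and one extra data cut. The landmark analysis ignores early admissions and drops early deaths from both cohorts (about 6% by week 10 under the assumptions above), a small loss of precision. It equalises the survival condition but not willingness or fitness to attend, so its result should stay supportive.
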